### Hypotheses and research questions

1.5

Hypothesis about the primary outcomes:**H1**Survivors in both treatment groups (Group 1 and Group 2) are expected to show a greater reduction in depression and anxiety symptoms than survivors in the TAU (Group 3) at post-treatment and 2-month follow-up.

Hypotheses about the secondary outcomes:**H2**Survivors in both treatment groups (Group 1 and Group 2) are expected to have greater improvements in cancer-related quality of life, coping, and fear of recurrence compared to survivors in the TAU (Group 3) at post-treatment and 2-month follow-up.**H3**Survivors in both treatment groups (Group 1 and Group 2) are expected to use more active coping strategies than survivors in the TAU (Group 3) at post-treatment and 2-month follow-up.**H4**A reduction in depression and anxiety symptoms of survivors in both treatment groups (Group 1 and Group 2) is expected to be mediated by the change in coping strategies after controlling for depression and anxiety levels at baseline.**H5**An improvement in cancer-related quality of life in both treatment groups (Group 1 and Group 2) will be mediated by the change in coping strategies after controlling for cancer-related quality of life at baseline.

The effects of carer access will be explored using the following research questions:

**RQ1.** Is there a difference in depression and anxiety scores between iCBT alone (Group 1) and iCBT with the carer access (Group 2) at post-treatment after controlling for baseline depression and anxiety scores?

**RQ2.** Is there a difference in perceived social support between iCBT alone (Group 1) and iCBT with the carer access (Group 2) at post-treatment after controlling for baseline perceived social support?

**RQ3.** Is there a difference in survivor-carer relationship outcomes (cancer-related communication quality and relationship quality) of survivors in iCBT with carer access between baseline and post-treatment?

**RQ4.** Is there a difference in survivor-carer relationship outcomes (cancer-related communication quality and survivor-carer relationship quality) of carers between baseline and post-treatment?

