### Sample size

2.4

The G-Power software programme was used to carry out power analysis and determine the sample size needed for three-group, pre-test, post-test, and follow-up design. The data from a randomised controlled trial of an iCBT programme for depression and anxiety among cancer survivors revealed a large within-between interaction effect size for the HADS-Total after comparing the pre-treatment and post-treatment scores of the iCBT and the TAU (Murphy et al., 2019). To calculate the sample size, we powered for the changes in the primary outcome (depression and anxiety symptoms, measured by the HADS-Total) when comparing the treatment groups (iCBT alone and iCBT with the carer access) with the TAU. Assuming a medium effect size (*f* = 0.30) for the pre, post, follow-up comparisons between iCBT alone, iCBT with carer access, and TAU with a power of 0.80 and significance level of α = 0.05, the sample size is calculated to be 27 breast cancer survivors in each group and 81 in total (54 in the iCBT group and 27 in the TAU group using 2:1 ratio). Considering the 25% attrition (Richards et al., 2018), 108 breast cancer survivors in total (*n* = 72 for iCBT and = 36 for TAU) will be recruited.

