#### Effectiveness analyses for primary and secondary outcomes

2.10.2

Linear Mixed Modelling (LMM) will be used to compare pre-treatment, post-treatment, and 2-month follow-up scores of the survivors in three groups (iCBT alone, iCBT with the carer, and TAU control) on the main outcome measure of depression and anxiety as well as secondary outcome measures including cancer-related quality of life, coping, and fear of cancer recurrence. The intention-to-treat (ITT) and per-protocol (PP) approach will be used to test the effectiveness of the treatment groups over the TAU control group. According to the ITT approach, participants who leave the study early or do not comply with the protocol are considered as belonging to the treatment arm they were originally randomised to. On the other hand, PP analytical approach does not include patients who violate the protocol, switch the allocation arm throughout the study, do not adhere to the assigned treatment or do not undergo to the scheduled assessments over time. Thus, it helps capture the “true” exposure to treatment. As suggested, the ITT will be used as the main method of analysis to determine effectiveness as it provides an unbiased estimate to treatment effect, and the PP will be used as a secondary and supportive analysis (Tripepi et al., 2020) to provide complementary information about the iCBT intervention. Restricted maximum likelihood (REML) estimation will be used to account for missing data due to participant drop-out. Significant effects will be followed up using pairwise contrasts comparing mean pre-treatment scores to post-treatment scores. Between-group (Hedges' *g*) and within-group (Cohen's *d*) effect sizes will be calculated using the pooled standard deviation and adjusted for sample size. For Hedges' *g* and Cohen's *d* an effect size 0.20 is considered small, 0.50 moderate, and 0.80 large.

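### The only stated follow-up contrasts depend on a significant effect and stop at post-treatment, so the iCBT v TAU comparison in H1 is either gated behind a less focused test or not specified

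*Protocol article*

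**What the plan says.** H1 (section 1.5) states that survivors in both iCBT groups "are expected to show a greater reduction in depression and anxiety symptoms than survivors in the TAU (Group 3"), and it covers both post-treatment and the 2-month follow-up. Section 2.4 says the sample size was set for the treatment groups against TAU on HADS-Total. The effect size entered, however, is an f of 0.30 "for the pre, post, follow-up comparisons between iCBT alone, iCBT with carer access, and TAU with a power of 0.80", which is a three-group quantity.

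Section 2.10.2 describes one effectiveness model, a linear mixed model of three groups over three time points. It says that ITT (main) and PP (supportive) will be used to test the treatment groups over TAU. It then gives its one rule on contrasts: "Significant effects will be followed up using pairwise contrasts", with the contrasts described as comparing pre-treatment means with post-treatment means. The next sentence plans between-group Hedges' g and within-group Cohen's d and attaches no condition to either. Sections 2.1 and 3 call the comparison of iCBT alone with iCBT plus carer access exploratory, because that split follows the survivor's preference.

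**The concern.** A directional hypothesis fixed in advance needs no prior significant result on a broader test. With three groups and three times, the group-by-time test has (3 − 1)(3 − 1) = 4 df. Two of these belong to iCBT v TAU, and two to Group 1 v Group 2, which the protocol treats as exploratory. Passing that test first makes the primary question depend partly on a question that is not primary.

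The stated contrasts also do not match H1. They cover pre to post only, so the 2-month part of H1 has no contrast. They may also be purely within-group, in which case no iCBT v TAU contrast is stated at all. What is at stake is some power for the primary comparison, and certainty about which estimate answers H1.

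**Working it through.** **The plan's own figures.** "the sample size is calculated to be 27 breast cancer survivors in each group and 81 in total", split as "54 in the iCBT group and 27 in the TAU group using 2:1 ratio", with 25% attrition. The inflation reproduces: 81/(1 − 0.25) = 108, 54/0.75 = 72, 27/0.75 = 36. The 81 itself cannot be settled, because neither the within-person correlation nor the power-programme option is given. At f = 0.30 and 80% power, a between-factors test needs 75 women at correlation 0.5 and 82 at 0.6. An interaction test needs 25 at correlation 0.5, or 69 to 72 under other effect-size conventions.

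**Inputs for the check.** From section 2.4: α = 0.05 and 27/27/27 evaluable women. Assumed: compound symmetry with within-person correlation ρ of 0.5 or 0.7; the same true effect d (in SD units) in both iCBT groups at post-treatment and at 2 months; complete data.

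**Effect sizes.** With group means (d, d, 0), f = d√(2/9) = 0.471d. So f = 0.30 corresponds to d = 0.30/0.471 = 0.636. The value d = 0.5 has support in section 1.2, which reports 0.50 against waiting list for the original programme. The value d = 0.8 is a more favourable case.

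**Gate.** Group-by-time F test with 4 and (81 − 3) × 2 = 156 df. The group sum of squares is 27 × (1/9 + 1/9 + 4/9)d² = 18d². The time pattern (0, 1, 1), centred, has sum of squares 2/3. Hence λ = 18d² × (2/3)/(1 − ρ) = 12d²/(1 − ρ).

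**Contrast.** Pooled iCBT (54) v TAU (27) on change from baseline to post-treatment, two-sided t test with 79 df. The standard error is √[2(1 − ρ)(1/54 + 1/27)], which is 0.236 at ρ = 0.5 and 0.183 at ρ = 0.7. The noncentrality is δ = d/SE.

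The gate and the contrast alone come from the noncentral F and t distributions. The chance that both are significant comes from simulation, so it carries up to about 1 point of error.

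| d | ρ | λ | Gate opens | δ | Contrast alone | Gate and contrast | Loss (points) |
|---|---|---|---|---|---|---|---|
| 0.5 | 0.5 | 6.0 | 46% | 2.12 | 55% | 38–39% | 16–17 |
| 0.5 | 0.7 | 10.0 | 70% | 2.74 | 77% | 63–64% | 13–14 |
| 0.636 | 0.5 | 9.7 | 69% | 2.70 | 76% | 62–63% | 13–14 |
| 0.636 | 0.7 | 16.2 | 91% | 3.48 | 93% | 88% | 5 |
| 0.8 | 0.5 | 15.4 | 89% | 3.39 | 92% | 86% | 6–7 |
| 0.8 | 0.7 | 25.6 | 99% | 4.38 | 99% | 98% | 1 |

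Splitting the 54 iCBT women 36/18 or 45/9, as preference might, changes these figures little.

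**If the contrasts are within-group only.** No arithmetic applies. H1 asks for a difference between groups in change at two times; the rule supplies pre-post comparisons at one.

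**The case against.** The strongest case against has four parts.

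- **No gate on iCBT v TAU is written.** The contrasts described are pre to post, section 2.10.2 names neither an omnibus nor an interaction test, and its ITT/PP sentence announces a test of iCBT over TAU without a condition. This stands in part. The 4-df gate is an inference, though the likely one for a three-by-three model. But the ITT/PP sentence names an analysis approach; it gives no contrast, time point or estimate.
- **A reader might infer that the primary comparison will often never be tested.** The documents do not support that. Near the planning value the gate opens in roughly 70 to 91% of trials, and at d = 0.8 in about 89 to 99%. Only below the planning value does it close often: at d = 0.5 it opens in 46 to 70%, at d = 0.3 in 17 to 28%.
- **A reader might infer that the reported effect will be inflated by a significance filter.** That would need estimates to be reported only when the gate opens, and the protocol does not say so; between-group Hedges' g is planned without a condition. Under such selection the inflation would be about 4 to 15% at d = 0.636 and 14 to 32% at d = 0.5, but this is hypothetical.
- **Naming the contrast is commonly left to an analysis plan, which is not shown.** This is fair for detail that is simply absent. Here the article states a rule, and as stated it does not serve H1.

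**Conclusion.** The point holds in a limited form. The only contrast rule in section 2.10.2 is conditional on significance and ends at post-treatment, while H1 is a planned iCBT v TAU comparison at two times. If the gate is the group-by-time test, it costs the post-treatment contrast about 5 to 14 points of power at the planning effect, 13 to 17 at d = 0.5 and 1 to 7 at d = 0.8. If the contrasts are within-group, H1 has no stated contrast. Under both readings the 2-month comparison lacks one.

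These sizes rest on assumed correlations of 0.5 to 0.7, equal effects in the two iCBT groups and at both times, complete data, and reading f = 0.30 as a spread of group means; the protocol gives no SD or correlation. Neither routine omission of the primary test nor a biased estimate can be claimed from the text.

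**What to change.** In section 2.10.2, replace the contrast rule with wording such as:

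> The pooled iCBT v TAU difference in change in HADS-T from baseline to post-treatment and from baseline to 2 months will be estimated from the ITT linear mixed model, tested, and reported with 95% confidence intervals, whatever the overall test shows. The same contrasts will be reported for the secondary outcomes as supportive results.

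The significance condition can stay, if wanted, for the exploratory pairwise comparisons among the three groups.

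The change takes a few sentences and no new data. It is not entirely free: more contrasts are shown, and with two time points for HADS-T the plan should also say which is primary or how multiplicity is handled. If an analysis plan already names these contrasts, aligning this section with it is enough.

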#### Analyses exploring the effects of carer access

2.10.3

LMM will be used to explore whether there are differences in depression and anxiety scores and perceived social support of survivors who used the iCBT programme alone and survivors who used the iCBT programme with carers having access at post-treatment. To account for the potential confounds, baseline levels of perceived social support will be controlled when comparing the iCBT alone and iCBT with the carer access groups. Those who have someone to care for them may perceive higher social support prior to the iCBT intervention and the initial levels may influence responses to the iCBT programme. LMM will also be used to evaluate whether there are differences in survivors' and their carers' communication quality and relationship quality scores at post-treatment after controlling for baseline scores.

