### Randomisation

2.5

Eligible participants will be randomly assigned to either iCBT intervention (n = 72) or treatment-as-usual control (*n* = 36) with a 2:1 ratio. Those who are assigned to iCBT group and have carers will be asked whether they will participate with or without their main carer. Participants will be assigned to iCBT alone or iCBT with carer access based on their preference and informed immediately about their group assignment. Survivors in the iCBT alone group (Group 1) will be using the iCBT programme by themselves, and survivors in the iCBT with the main carer access group (Group 2) will be using the same programme, but their main carers will also have access to the programme content using a separate username and password. Participants in the treatment-as-usual control group (Group 3) will continue their usual care and will not receive the iCBT programme during this study. They will fill out the same measures as the other two groups at pre-treatment, post-treatment, and 2-month follow-up.

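### For the exploratory carer-access comparison, section 2.10.3 omits the baseline HADS-T covariate that RQ1 names, and its comparator includes women who had no carer to give access to

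*Protocol article*

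**What the plan says.** Section 1.5 poses RQ1 as the difference in depression and anxiety between Groups 1 and 2 "at post-treatment after controlling for baseline depression and anxiety scores". RQ2 asks the same of perceived social support, "at post-treatment after controlling for baseline perceived social support". Each question names the baseline value of its own outcome.

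Section 2.10.3 handles both outcomes in one sentence, which begins: "LMM will be used to explore whether there are differences in depression and anxiety scores and perceived social support of survivors who used the iCBT". The contrast there is between women with and without carer access. It then says that "baseline levels of perceived social support will be controlled when comparing the iCBT alone and iCBT with the carer access groups". The reason given is that "Those who have someone to care for them may perceive higher social support prior to the iCBT intervention". A later sentence provides for "communication quality and relationship quality scores at post-treatment after controlling for baseline scores", which concerns the survivor-carer relationship measures and not HADS-T.

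On how the groups arise, section 2.5 states: "Those who are assigned to iCBT group and have carers will be asked whether they will participate with or without their main carer". It continues: "Participants will be assigned to iCBT alone or iCBT with carer access based on their preference". Section 1.4 fixes the number of groups at three. Section 2.2 does not make having a carer a condition of entry for survivors. Presence of a carer is recorded at screening (2.9.1.1) and is listed among the baseline characteristics to be described (2.10.1).

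**The concern.** Two sections give different covariates for the same comparison. This comparison has no randomisation behind it, so the covariate list carries most of the weight. Baseline HADS-T is the outcome variable measured earlier. If women who choose carer access start at a different level of distress, a post-treatment comparison without that baseline carries part of the starting difference into the apparent effect of access.

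The second issue is who stands in the comparator. Everyone in Group 2 has a carer. Group 1 holds women who have a carer and declined access together with women who have no carer. Aim (e) in section 1.4 is about the effect of carer access, but a difference between the groups as formed may equally reflect living with or without a carer.

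**Working it through.** The plan gives no figure to reproduce here. The check is a comparison of the text, followed by an illustration on assumed values.

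**Covariates side by side**

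| Question | Section 1.5 | Section 2.10.3 |
|---|---|---|
| RQ1: depression and anxiety, Group 1 v 2 | baseline depression and anxiety | baseline social support |
| RQ2: social support, Group 1 v 2 | baseline social support | baseline social support |

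RQ2 is consistent. RQ1 is not, and the mention of baseline scores later in 2.10.3 belongs to other outcomes.

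**Composition of Group 1**

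1. Survivors without a carer are eligible (2.2).
2. In the iCBT arm, only those with a carer are offered the choice (1.4, 2.5).
3. There are three groups, so a woman without a carer who is randomised to iCBT can only be in Group 1.

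Let p be the share of Group 1 without a carer. Let A, D and N be the adjusted mean post-treatment scores of women who gave access, women who had a carer and declined, and women with no carer. Then

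Group 2 − Group 1 = A − [(1 − p)D + pN] = (A − D) − p(N − D).

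Only A − D concerns giving access, and even that still carries preference. The second term is the effect of having no carer. It vanishes only if p = 0 or N = D after adjustment. The documents give neither p nor N − D, so no size can be put on this part.

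**Illustration of omitting baseline HADS-T** (all inputs assumed, true access effect zero)

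Bias left = slope of post-treatment on baseline HADS-T at fixed social support × baseline gap at equal social support.

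- Slope 0.6 (pre-post correlation 0.6, social support adding nothing once baseline HADS-T is known): gaps of 0.2, 0.3 and 0.5 SD give 0.12, 0.18 and 0.30 SD.
- If social support correlates −0.3 with HADS-T at both times: slope = (0.6 − 0.09)/(1 − 0.09) = 0.51/0.91 = 0.56. The same gaps give 0.11, 0.17 and 0.28 SD.

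The range is therefore roughly 0.1 to 0.3 SD.

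A large simulation agrees. It used a pre-post correlation of 0.6 and a baseline HADS-T to social support correlation of −0.3, with the choice of access depending on both. Results for two strengths of selection, in SD:

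| Overall baseline gap | Crude difference | Adjusted for social support only | Baseline HADS-T added |
|---|---|---|---|
| −0.41 | −0.25 | −0.16 | about 0 |
| −0.56 | −0.34 | −0.26 | about 0 |

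The last column is near zero because the simulation contains no other confounder. The trial may well have others.

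**Scale.** Section 2.4 plans for 54 evaluable women in the iCBT arm. Power for a true 0.5 SD difference is 0.45 with a 27/27 split, 0.41 with 36/18 and 0.30 with 44/10. The splits are assumed, since preference determines them.

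**The case against.** The strongest reply is that the sections do not contradict each other. Section 2.10.3 introduces social support as a potential confounder with its own rationale. It does not say that this is the only covariate, nor does it withdraw RQ1's. Read together, RQ1 would adjust for both, which is what one would want. That reading is available and may be what was intended. A reader might infer that the plan has decided against adjusting for baseline HADS-T; the text does not support that. What stands is that the analysis section does not say so, and either list or both could be chosen after the data are seen.

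Second, section 2.10.2 uses mixed models on repeated scores, so baseline HADS-T could enter 2.10.3 as an outcome. This is possible, but 2.10.3 describes a post-treatment difference, and a change contrast is not RQ1's baseline-adjusted contrast. With a 0.3 SD gap and slope 0.6, a change contrast would carry (0.6 − 1) × 0.3 = −0.12 SD, of opposite sign to the 0.18 SD above. Even the direction of the error thus depends on the model chosen.

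Third, section 2.1 declares the carer-access analyses exploratory because allocation is by preference, and section 3 promises cautious interpretation. Baseline tables will show carer status. All this is true and limits the weight of the point. The reason that section 3 gives for caution, however, is low power, and describing an imbalance does not remove it from the contrast.

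Fourth, restricting to women with carers shrinks an analysis that section 3 already calls possibly underpowered, and self-selection among them remains. Both statements are correct, and the fix should acknowledge them.

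**Conclusion.** The point holds as a clarification of covariates and a limitation of the comparator. RQ1 names a covariate that the analysis section does not repeat. The Group 1 versus Group 2 contrast as written cannot separate having a carer from giving the carer access, and the single social-support covariate does not do so either.

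The size is illustrative: roughly 0.1 to 0.3 SD if baseline HADS-T is omitted altogether, for baseline gaps of 0.2 to 0.5 SD at equal social support and a pre-post correlation of about 0.6. None of these values comes from the documents. If both covariates were always intended, this part of the bias does not arise.

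A reader might also infer that the trial's main result is at risk. It is not: randomised iCBT versus TAU does not depend on this contrast. Nor would the fix make the carer-access comparison unconfounded, since preference remains. RQ2's covariate is already consistent and needs no correction.

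**What to change.** In section 2.10.3:

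- State that RQ1 adjusts for both baseline HADS-T and baseline MOS-SSS. RQ2 keeps baseline MOS-SSS.
- Make the carer-access contrast among iCBT survivors who report a main carer at baseline. Report iCBT women without a carer separately, or show the contrast against all of Group 1 alongside.
- Say plainly that confounding by preference remains among women with carers, and that this, as well as low power, is a reason for caution.

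No new data are needed: HADS-T, MOS-SSS and carer status are all collected before randomisation. The cost is a smaller comparator and less precision, to an extent that depends on how many iCBT women have no carer.

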#### Qualitative analyses

2.10.4

Responses of survivors and carers to helpful and unhelpful aspects of therapy in the HAT will be qualitatively analysed using thematic analysis with an inductive approach by the primary researcher [name]. Inductive analysis is a process of data coding without relying on a pre-existing coding frame or the researcher's theoretical commitments or analytic preconceptions (Braun and Clarke, 2006). To provide insight into participants' experiences, common themes, and patterns concerning helpful and unhelpful aspects of the programme, and their impact on survivors will be identified in this analysis. After the interpretation of the raw data, codes will be separated into helpful aspects, unhelpful aspects, and their impacts, and then initial themes will be generated, coded, and finally given names with clear definitions. These codes will be reviewed by another researcher who has experience in qualitative analysis to discuss the identified patterns and themes in the dataset. Quantitative data from the SAT will be analysed using descriptive analysis and the qualitative responses on the second part of the scale will be analysed using thematic analyses following the same procedure in the HAT analysis.

